
### Data analysis

All data will undergo statistical tests, analysis will be based on baseline and follow-up data. In case of missing value, statistician will take out corresponding countermeasures in according to the provenance mechanisms of the missing data and the practical situation. Quantitative data will be described by “mean ± standard deviation” or “Median (Range)” and compared using Student’s t test, analysis of variance (ANOVA) and nonparametric test between two or multiple groups. Data for repeated measurements will be compared using multivariate analysis of variance (MANOVA) or trend test. Qualitative data is described by “Frequency (percentage)” and analyzed by the chi-square test (or Fisher’s exact test, if appropriate), and nonparametric test in differentiation among the groups. Pearson correlation or Spearman rank correlation will be used for correlation analysis. Multivariate statistical analysis including multiple linear regression, logistic regression, cox proportional hazards model, factor analysis, path analysis will be implemented in multivariate analysis or modeling process according to the data type. In case of multiple dimensional correcting issues of confounding factors, which can not be adjusted by multivariate model, then propensity score matching (PSM) or inverse probability weighting (IPW) will be applied. Such as Nomogram or classification and regression tree (CART) will be implemented to establish predictive models which could predict patients’ response to drugs (curative effects) in different diseases and proper subgroup analysis in clinically important indicators will be applied to find out high-benefit population. The models will be evaluated using the receiver operating characteristic-derived area under the curve (AUC) or Harrell concordance index (C-index), calibration plot, and decision-curve analyses (DCAs).

For Pharmacogenomics and pharmacometabolomics, two kinds of statistical analysis will be implemented: 1) multivariate statistical analysis such as random forest, support vector machine learning, principal component analysis (PCA), partial least square discriminant analysis (PLS-DA), orthogonal partial least square discriminant analysis (OPLS-DA). 2) univariate statistical analysis, correlation analysis, and the regression analysis will be used. The predictor-ranking model will be determined by significant cutoff values (*p* < 0.05). All of data will be analyzed by R language (http://cran.r-project.org/) or SPSS (version 19.0) or SAS (University Edition) software.

To enhance comparability between outcome measures, we will select some comparable subgroups for analysis. Subgroups analysis includes comparison between healthy controls (from Ophthalmic Bio-bank of Shanghai Jiaotong University) and AMD patients, PCV patients, and CNV secondary to PM patients respectively for detecting the disease biomarkers; comparison between AMD, PCV and CNV secondary to PM patients to analyze the different signatures within different macular neovascular diseases; comparision between patients who have good response and who have no response to Conbercept in AMD patients, PCV patients, CNV secondary to PM patients respectively to explore the potential predictors of patients’ response to Conbercept treatment.

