### Main outcome measures

#### Primary outcome

The primary outcome is visual changes primarily recorded as best-corrected visual acuity (BCVA) in EDTRS letters at V2, V3, V4, and V5 minus baseline vision (V1). The efficacy was graded as significantly effective (visual improvement ≥15 letters in EDTRS); effective (visual improvement ≥5 letters and < 15 letters in EDTRS); invalid (visual improvement < 5 letters and visual reduction< 5 letters in EDTRS); deterioration (visual reduction≥5 letters in EDTRS) [15]. Moreover, patients graded as significantly effective and effective that is BCVA improvement≥5 letters in EDTRS are defined as having response to Conbercept treatment and the response rate (the rate of patients graded as significantly effective and effective) will be assessed in the whole study population and in each diseases.

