### Quality control and management

We have made SOPs, videos and OC/RDC system to train all staffs involved in this study how to collect data, and deal with blood sample. The apparatus applied to our study have been certificated by CFDA. All prescribed drugs are from hospital pharmacy, and the empty bottle of Conbercept after injection will be retrieved to ensure the dosage used.

Data Management: Clinical information should be timely, accurately and completely recorded and entered into the CRF on national network of EDC, maintaining confidentiality in accordance with the local law for data protection. The electronic CRF should be consistent with the original medical records. All adverse events, concomitant medications should be documented, serious adverse events should be reported to the relevant authorities within 24 h.

Follow-up management: Follow-up should be conducted according to required time point under the rules. The investigators should enroll in local patients or patients who plan to have regular and long-term follow-up in the hospital, and the rate of lost to follow-up should be controlled below 20%. These procedures would help to minimize possible bias.

Center management: All researchers will be checked for the qualification, and then be trained to make sure they are familiar with the study protocol and will carry out the study strictly. Each center should appoint a clinical research coordinator (CRC) for quality control, making sure the CRF form timely recorded, assisting the check and inspection, drug reception, storage, distribution and checking procedures. CRC should report to PI when they found abnormal data or non-compliances to the protocol.

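### The only methods named for repeated BCVA are MANOVA or a trend test, and no named analysis accounts for the 43 centres

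*Protocol article*

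**What the plan says.** All points are from the protocol article.

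- **Primary outcome.** The outcome is the BCVA change from V1 at four follow-up visits, V2 to V5. A response rate (gain of at least 5 letters) is to be assessed overall and within each disease.
- **Data analysis, repeated data.** "Data for repeated measurements will be compared using multivariate analysis of variance (MANOVA) or trend test". The sentence does not name BCVA, but the primary outcome is a repeated measurement and falls under it. The trend test is not described further.
- **Data analysis, group comparisons.** Quantitative data are "compared using Student’s t test, analysis of variance (ANOVA) and nonparametric test between two or multiple groups". Frequencies are compared by chi-square or Fisher's exact test.
- **Data analysis, missing values.** "In case of missing value, statistician will take out corresponding countermeasures in according to the provenance mechanisms of the missing data and the practical situation". No method is named.
- **Study design and objectives; Table 1.** Visits have a window of 7 days either side, including the one at day 360. A return outside the window, or a missed visit, leads to registration by telephone.
- **Quality control and management.** For follow-up, "the rate of lost to follow-up should be controlled below 20" percent.
- **Participants and recruitment.** More than 5000 patients come from 43 centres whose intake depends on their capacity. Centre appears in none of the analyses listed.

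**The concern.** Standard MANOVA needs the full set of visits for each patient. With no imputation, one missing visit removes everything that patient contributed. The protocol's own rules make gaps likely: narrow windows, telephone contact that cannot supply a measured letter score, and a tolerated loss of up to 20%. The study is justified by how well it represents routine practice, so an analysis restricted to patients who attended every visit would work against its purpose if attendance is related to vision.

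The named t test, ANOVA and chi-square test treat patients as independent. Patients at one centre share prescribers, treatment habits and case mix, so their outcomes are likely to be correlated. An interval for the overall mean change or response rate that ignores this is too narrow.

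**Working it through.** The article gives no power, effect size, standard deviation or interval for the 5000 patients, so there is no stated figure to reproduce. The steps below are illustrations.

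**Inputs from the article:** N = 5000 and 43 centres (Participants and recruitment); four follow-up visits (Table 1); loss ceiling d = 0.20 (Quality control and management).

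**Assumed inputs:** share p of further visits missed independently among retained patients, 5% or 10%; intra-centre correlation (ICC) 0.01 to 0.05; equal centre sizes; response rate 50%.

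**1. Patients with all of V2 to V5.** Complete cases = N × (1 − d) × (1 − p)^4.

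| p | Calculation | Complete cases |
|---|---|---|
| 0 | 5000 × 0.80 | 4000 |
| 5% | 4000 × 0.8145 | 3258 (65%) |
| 10% | 4000 × 0.6561 | 2624 (52%) |

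**2. Can this bias the estimate?** A simulation of 400,000 patients used a standard deviation of 15 letters, a correlation of 0.7 between visits, and a chance of loss that rose after a poor previous change. By V5, 22.6% were lost. The true mean change at V5 was 7.0 letters. Complete cases gave 7.7, and an estimate using all observed visits under missing at random gave 7.0. The upward sign was built in by the assumed dropout; loss concentrated among patients doing well would push the other way. The example shows that bias is possible, not how large it will be here.

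**3. Centre clustering.** Mean centre size m = 5000 / 43 = 116.3. Design effect = 1 + (m − 1) × ICC. Naive half-width = 1.96 × √(0.25 / 5000) = 1.39 points; the corrected value is this times the square root of the design effect.

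| ICC | Design effect | Effective N | Half-width (points) |
|---|---|---|---|
| 0.01 | 2.15 | 2323 | 2.03 |
| 0.02 | 3.31 | 1513 | 2.52 |
| 0.05 | 6.76 | 739 | 3.60 |

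Unequal centre sizes would generally raise these values. For contrasts made within centres the inflation is smaller.

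**4. Baseline, only if diseases are contrasted on BCVA.** Change-score and baseline-adjusted contrasts differ by (1 − ρ) × the baseline difference, where ρ is the correlation of baseline with follow-up. For an assumed difference of 10 letters and ρ from 0.5 to 0.8, the two differ by 5 to 2 letters. The response threshold is 5 letters.

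**The case against.** The strongest reply is that the article leaves room for a sound analysis. It condenses a fuller protocol, and the analysis plan is not shown.

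- **Complete-case analysis is not a stated rule.** A reader might infer that patients with a missed visit will be dropped. The missing-data sentence promises handling that depends on the mechanism, and MANOVA after imputation is compatible with it. This stands: deletion is what un-imputed MANOVA does by default. The sentence fixes no method, however, so it does not remove the risk.
- **Only MANOVA has this property.** A reader might extend it to the t test and ANOVA. Applied to the change at one visit, those lose only patients without that visit.
- **Baseline is not ignored.** A reader might infer that it is. The outcome subtracts V1, and the article adds: "Multivariate statistical analysis including multiple linear regression, logistic regression, cox proportional hazards model, factor analysis, path analysis will be implemented". For confounding that such models cannot handle, "then propensity score matching (PSM) or inverse probability weighting (IPW) will be applied". Baseline BCVA, and centre too, could enter these analyses, although neither is named. Leaving the covariate list to an analysis plan is ordinary.
- **Confounded disease comparisons are not shown.** The article states no BCVA contrast between diseases and does not say that the diseases start from different vision; the comparison across diseases in its subgroup paragraph concerns biomarker signatures. Across non-randomised groups, change scores and baseline adjustment also answer different questions, and the choice between them is debatable.
- **The magnitudes are not the protocol's.** The missed-visit rate, ICC and ρ are all assumed, and the article states no interval of 1.4 points. Even a half-width of 3.6 points may be adequate for a descriptive study.

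What the reply does not answer is that the methods named for repeated data are a poor fit for incomplete follow-up, and that nothing named handles centre.

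**Conclusion.** The point holds for two parts of the plan: the method for repeated measurements and the missing allowance for centre. It is an improvement that should be made to a stated choice, not a flaw that invalidates the study.

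The figure of about 4000 patients needs only the protocol's loss ceiling and no imputation. The figures of about 3260 and 2620 also need independent missed visits at assumed rates. The design effect of about 2.2 to 6.8, and half-widths of about 2.0 to 3.6 points instead of 1.4, need an assumed ICC of 0.01 to 0.05, equal centre sizes and a response rate near 50%. They apply to overall summaries more than to within-centre contrasts.

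A reader might go further and conclude that the plan will overstate real-world benefit. The document does not support that: it gives no information on how loss relates to vision, so neither the direction nor the size of any bias can be derived.

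**What to change.** 1. Replace MANOVA with a linear mixed model for the repeated BCVA outcome at V2 to V5, using all available visits. Include visit, disease and disease-by-visit effects, an unstructured within-patient covariance and a random centre effect. Every patient with at least one follow-up BCVA then contributes.
2. Report response rates, overall and by disease, with centre-clustered (robust) standard errors or from a mixed logistic model.
3. Add a sensitivity analysis in which patients who drop out are allowed to differ from those who stay, since the mixed model relies on missing at random.
4. If disease groups are contrasted on BCVA, report a baseline-adjusted contrast beside the unadjusted change.

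The data to be collected do not change, and R or SAS is already planned. The cost is a little more analysis work and wider intervals for the overall rates.

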Among subjects, 500 patients will be selected to conduct pharmacometabolomics analysis compared with 500 healthy volunteers for detecting disease-associated metabolites. After the evaluation of patients’ curative parameters (listed below), preliminary pharmacogenomics and pharmacometabolomics analysis will be carried out. We will pick up 500 patients, half of them have good response from significant effective group and half have no response from deterioration group, their blood samples will be analyzed by pharmacogenomics and pharmacometabolomics to find out response-associated predictors, and then the predictors of patients’ response to Conbercept will be further validated in all of the recruited subjects. Figure 1 is the study design flow.

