### Participants and recruitment

More than 5000 patients will be recruited from 43 ophthalmic centers in china that suffer from AMD, PCV, and PM (List of Ophthalmic Center in Additional file 3). And it is the first time for them to receive ocular injection of Conbercept. Doctors in outpatient clinic who diagnose and prescribe are independent of the investigators in this study. The 43 ophthalmic centers cover most regions of China. The recruitment capacity of each center will be mainly depended on the daily outpatient and registration capacity, as well as follow-up conditions. Participation is voluntary and consent is obtained before the procedures. Until now, the recruitment and primary pharmacogenomic analysis is ongoing and 3055 patients have been recruited.

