#### Secondary outcome

The changes of retinal edema will be evaluated by central fovea retinal thickness (CRT in μm) at V2, V3, V4 and V5.The different therapeutic regimens of Conbercept prescribed by doctors and applied on different diseases in real-world clinical practice will be assessed, including number of treatments, frequency of injection (times per year), interval time (months).Response-related factors for Conbercept to macular neovascular diseases after 3 months’ treatment will be examined. We will compare the macular leakage area (mm^2^) and the CNV area (mm^2^) to baseline in FFA between patients who response to Conbercept treatment and patients with no response, and their relationship with the responders and nonreponders will be further analyzed.The potential biomarker of patients’ response to Conbercept will be investigated by pharmacogenomics and pharmacometabolomics as mentioned above in study design. The genomic variation between patients who respond to Conbercept treatment and patients who have no response to Conbercept drug treatment will be detected. Conbercept-sensitive associated Single Nucleotide Variations (SNVs) will be picked out by comparing the data of single nucleotide polymorphisms dbSNP and hapMap Database to remove common single nucleotide polymorphisms (SNPs) or SNVs information. Then we will design gene panel based on Next Generation Sequencing to validate the Conbercept-sensitive genomic regions among the whole study population. Besides, prediction model will establish to figure out Conbercept-sensitive genotype in macular neovascular diseases. For pharmacometabolomics studies, blood samples of patients and healthy volunteers will be analyzed by mass spectrometry to primarily screen disease-associated metabolites. The associations of genotype and metabolites with clinical endpoint will be assessed and further validated in the whole study population. Those signatures (gene/ metabolites) will be considered to be predictors of patients who will possibly have good response to Conbercept treatment, and those in non-responders will be recognized as potential predictors of patients who do not respond to Conbercept. Finally, we will build an Oracle database about macular neovascular diseases based on clinical information, pharmacogenomics, and pharmacometabolomics.Safety data: adverse events (AE) and severe adverse events (SAE) were defined according to other large-scale clinical trial on intravitreal injection of anti-VEGF drugs [14–16]. AE and SAE need to be recorded, and their relevance to drug or procedures will be estimated. The number and percentage of AE and SAE in the whole study population and in each disease will be calculated.

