Other anti-VEGF drugs such as ranibizumab or bevacizumab have been studied in treating PCV and CNV secondary to PM, and they had demonstrated effects on improving visual acuity and CRT [21–23]. However, the mechanisms of Conbercept in inhibiting VEGF function is different from the other anti-VEGF drugs, and whether the newly-developed drug is safe and efficacious for PCV and CNV secondary to PM have not been estimated. In our study, numerous clinical data we collected may provide convincing evidence for applications of Conbercept in PCV and CNV secondary to PMand may benefit further RCTs.

In the present study, we will use pharmacogenomics and pharmacometabolomics to investigate the biomarkers on the efficacy of Conbercept treatment. It has been reported that some patients have poor or no response to anti-VEGF drugs [24–26], and extensive and repeated administration of anti-VEGF drugs often leads to unnecessary wastes. Previously, researchers had found that gene polymorphism is associated with AMD patients’ response to intravitreal injection of anti-VEGF drugs and therapeutic regimen [27]. However, most of the studies analyzed assessed limited number of SNPs and their interactions with patients’ response to ranibizumab, the number of injections needed to maintain visual gains [27]. In this study, whole genome information may provide much more important data. Besides, there are no reported study involving pharmacometabolomics on Conbercept treating AMD, PCV, and CNV secondary to PM. In our study, we will select some patients for whole-genome sequencing and pharmacometabolomics analysis, then validate among larger populations. We expect to find new predictors of patients’ response to Conbercept, and the outcome would help doctors to treat these patients effectively, further develop individualized therapy, and improve patients’ compliance.

Although we will comprehensively investigate the clinical data, genome information, and metabolic factors of Chinese population, the current study still lacks clinical information in other human races. Therefore, further worldwide clinical studies are still needed to testify the above-mentioned results in other human races.

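### An uncorrected p < 0.05 is the only cut-off stated for a whole-genome and metabolomic predictor screen, and the validation step only partly makes up for it

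*Protocol article*

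**What the plan says.** All references are to the protocol article.

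- **Cut-off.** Under Data analysis, the omics paragraph lists machine-learning and projection methods and then says that "univariate statistical analysis, correlation analysis, and the regression analysis will be used". It closes with the selection rule: "The predictor-ranking model will be determined by significant cutoff values (*p* < 0.05". This is the only threshold given for either omics layer. Bonferroni, false discovery rate, genome-wide and permutation control are not mentioned anywhere.
- **Breadth.** The Discussion says "we will select some patients for whole-genome sequencing and pharmacometabolomics analysis, then validate among larger populations". Secondary outcome adds mass-spectrometry metabolite profiling. Data analysis repeats the responder comparison within AMD, PCV and myopic CNV, and adds comparisons with healthy controls and between diseases.
- **Discovery sample.** Study design and objectives: "We will pick up 500 patients, half of them have good response from significant effective group and half have no response from deterioration group".
- **Variant filter.** Secondary outcome uses dbSNP and HapMap "to remove common single nucleotide polymorphisms (SNPs) or SNVs information". The number of variants left is not stated.
- **Validation.** Secondary outcome: "Then we will design gene panel based on Next Generation Sequencing to validate the Conbercept-sensitive genomic regions among the whole study population". Study design and objectives likewise validates in everyone recruited. Neither place gives a threshold or sets the discovery patients aside.
- **Use of the result.** Secondary outcome treats the resulting signatures as predictors of good response or of non-response. The Discussion expects them to guide individual treatment.

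**The concern.** A per-test level of 0.05 lets through one null marker in twenty. That is tolerable for a few pre-chosen markers, but not for a screen of the whole genome and a metabolite profile run several times over. Followed as written, the rule fills the candidate list mostly with chance findings.

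The burden then falls on validation. If validation is not independent of discovery and has no strict threshold of its own, some chance findings go on to be reported as markers of response to Conbercept. Clinicians might then use them to decide whom to treat, which is what the article hopes for.

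This is more than a detail that an article may leave to the analysis plan. The article states a cut-off, and that cut-off does not suit the screen it governs.

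**Working it through.** The article gives no error-rate or power calculation for the omics part, so there is no figure of its own to reproduce.

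**Inputs from the article:** cut-off 0.05; discovery 250 v 250; total recruitment more than 5,000; validation in all recruited patients; loss to follow-up to be kept below 20%.

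**Assumed inputs:** testable variants M after the filter, 100,000 to 10 million; metabolites, 500 to 2,000; validation also at two-sided p < 0.05.

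**Step 1. First-stage passes with no true effect** = 0.05 × M. For metabolites: 0.05 × 500 = 25 and 0.05 × 2,000 = 100 per comparison. Repeating a comparison of the same size in three diseases triples the expected count. The chance of at least one false hit in m independent tests is 1 − 0.95^m: 0.64 at m = 20 and 0.994 at m = 100.

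**Step 2. Effect of a conservative test on rare variants.** With Fisher's exact test at 250 v 250, five carriers all in one arm give p of about 2 × 0.5^5 = 0.06, so a variant with five or fewer carriers can never pass. At the carrier counts checked from 6 to 200, the exact size is 0.7% to 3.7%, so 0.05 × M overcounts. An uncorrected chi-square test has no such bound; its size is 12% at four carriers.

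**Step 3. Validation that includes the discovery patients.** Let f be the share of validation information that comes from the discovery 500. With equal information per patient, f = 500/5,000 = 0.10. Under the null, Z_all = √f × Z_disc + √(1 − f) × Z_rest. The quantity needed is P(|Z_all| > 1.96 given |Z_disc| > 1.96). Simulation with 2 million draws gives:

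| Patients in validation | f | False candidate confirmed |
|---|---|---|
| independent set | 0 | 5% |
| 5,000 | 0.10 | 10.4% |
| 4,000 (20% lost) | 0.125 | 11.5% |
| 3,055 (recruited so far) | 0.164 | 13.8% |

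If the extreme responders carry more information than their share of the sample, the rate rises: 15.8% at f = 0.2 and 21.4% at f = 0.3.

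**Step 4. Both stages together.** Overlapping validation leaves 0.05 × 0.104 = 0.52% of M; independent validation leaves 0.05 × 0.05 = 0.25%.

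| M | Pass stage 1 | Also pass an independent p < 0.05 | Also pass with 10% overlap |
|---|---|---|---|
| 100,000 | 5,000 | 250 | about 520 |
| 1 million | 50,000 | 2,500 | about 5,200 |
| 10 million | 500,000 | 25,000 | about 52,000 |

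The last two columns are ceilings, because they assume that every first-stage pass goes on to the gene panel. A smaller panel of k false candidates would confirm about 0.104 × k.

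**The case against.** The strongest reply has four parts.

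1. **The text does not say the p-values are unadjusted or per marker.** A 0.05 cut-off on adjusted p-values would fit the words, and random forest or PLS-DA do not select by p-value. This stands as an ambiguity. It does not remove the point: the same paragraph lists univariate and regression tests, gives 0.05 as the deciding value, and no adjustment appears anywhere.

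2. **Validation comes before any predictor claim.** This stands in part. A reader might infer that the plan will deliver tens to hundreds of thousands of false predictors. The documents do not support that. The number of tests is not stated, the common-variant filter lowers it by an unknown amount, the large counts are first-stage candidates, and only what goes on the gene panel can be confirmed. For metabolites the first-stage count is tens to about a hundred per comparison.

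3. **The work is secondary and exploratory.** The visual acuity and safety outcomes are indeed untouched. But the article intends to call the surviving signatures predictors and hopes that they will steer treatment, so the error rate still matters.

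4. **Regional ancestry.** Because "The 43 ophthalmic centers cover most regions of China", a reader might infer that uncorrected ancestry differences are a further stated error. They are not. Data analysis lists regression, principal components and confounding adjustment, and geographic spread alone does not show that ancestry is related to response.

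**Conclusion.** The point holds as a badly fixed rule: 0.05 is the only stated cut-off for a screen of this breadth, and the validation step is a partial safeguard because it has no threshold and reuses the discovery patients.

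The size is conditional on assumed test counts. Under the null it is about 5,000 to 500,000 first-stage variant passes for 100,000 to 10 million testable variants (fewer with exact tests on rare variants), and 25 to 100 metabolite passes per comparison for 500 to 2,000 metabolites. The doubling of false confirmation, from 5% to about 10%, assumes that p < 0.05 is reused, that 5,000 patients are validated and that each carries equal information. A smaller validation set makes it worse. How many false predictors would finally be declared cannot be derived from the article.

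**What to change.** Replace the cut-off with a staged rule:

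1. Use the 250 v 250 step only to rank candidates and choose a panel of k markers, with k fixed before validation data are examined.
2. Confirm only in patients outside the discovery 500, at 0.05/k, with the disease-specific tests counted. For example, k = 100 gives 0.0005 for one pooled test per marker, or 0.05/300 = 0.00017 if each marker is tested in three diseases.
3. Claim genome-wide significance from discovery alone only at a genome-wide threshold. Bonferroni gives 5e-7, 5e-8 and 5e-9 for 100,000, 1 million and 10 million tests.
4. Control the false discovery rate at 5% for metabolites.
5. State whether any 0.05 elsewhere applies to raw or adjusted p-values, and to which methods.

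**Cost.** Recruitment does not change, but the validation wording in Study design and objectives and in Secondary outcome must change as well as Data analysis. Validation shrinks from 5,000 to 4,500 patients before losses, and fewer markers will be declared.

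Power for rare variants, which are what the filter leaves, will be low. Take 4,500 patients split 60/40 (assumed), so 5,400 and 3,600 alleles, with allele frequency 0.03 and odds ratio 1.3. The second frequency is 0.039/1.009 = 0.0387, the difference 0.0087 and its standard error 0.0039, so z is about 2.24 against a critical value of 3.48 at 0.0005. Power is about 11%. The article should acknowledge this limit.
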